#### Patient experience (secondary outcome)

We use Hospital Consumer Assessment of Healthcare Providers and Systems (HCAHPS) global ratings of hospital care [44]. Data will be reported as the number and percentage of patients giving the most favorable rating (“top box”) to patient satisfaction questions. Each year, the research nurse will obtain data for patients admitted to study units, excluding those transferred from other hospitals and those initially admitted to other units. Research nurses will de-identify data prior to importing it into REDcap.

#### Efficiency measures (secondary outcomes)

We assess efficiency of care using hospital length of stay (LOS) and 30-day readmissions. LOS will be reported as median (IQR) as data are typically skewed in distribution. As for patient experience data, the research nurse will obtain data on a yearly basis for patients admitted to study units, excluding those transferred from other hospitals and those initially admitted to other units. Research nurses will de-identify data prior to importing it into REDcap. This data will include information on patient age, sex, race, payer, admission source, primary diagnosis, secondary diagnoses, type of admission (i.e., observation vs. inpatient), and discharge destination (i.e., home vs. other).

#### Teamwork climate

First, we will compare baseline teamwork climate scores to post-implementation scores for Phase I Implementation Units. We will use two-sample t tests (for all professionals) and paired t tests (for professionals responding to both surveys). Data is expected to be normally distributed based on prior studies [36, 39]. Second, we will compare baseline teamwork climate scores to post-implementation scores for Phase II Implementation Units using two-sample t tests (for all professionals) and paired t tests (for professionals responding to both surveys). Third, we will conduct a two group pretest-posttest analysis using multiple linear regression with teamwork score as the outcome variable. The model will compare the change in teamwork climate from baseline to post-implementation in Phase I Implementation units to the change in Phase II Implementation units across 2 baseline periods. The model will use an interaction term defined as unit type (Phase I vs. Phase II) multiplied by the intervention period (year 1 vs. year 2) to examine the change in teamwork climate (i.e., difference-in-differences analysis). We will use standard errors robust to the clustering of professionals within each hospital.

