### Outcome measures

#### Teamwork climate (primary outcome)

We will assess teamwork climate using the Safety Attitudes Questionnaire (SAQ) developed by Sexton et al. [38] The SAQ teamwork climate domain includes 14 questions, generates a score from 0 to 100, and has been sensitive to change in prior studies assessing microsystem change [36, 39]. Similar to prior studies, we also ask respondents to rate the quality of collaboration experienced with each professional type [6, 40]. We administer the survey annually (years 1 through 4) to all nurses, nurse assistants, physicians, pharmacists, social workers, and case managers on study units. Names and email addresses of professionals on study units are obtained and the survey administered by the central coordinating center using REDCap. Site leaders promote completion of the survey and non-responders receive up to 5 reminder emails to optimize response rates.

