### Power and sample size

#### Teamwork climate

Prior research using similar interventions has shown that teamwork climate increases for all professionals, but the improvement is greatest for nurses [36, 39, 40]. Therefore, we estimated a target sample size of nurses using results from prior studies. A sample size of 68 achieves 90% power to detect a mean of paired differences of 4.0 with an estimated standard deviation of differences of 10.0 and with a significance level of 0.05 using a two-sided paired t-test [46]. This sample size reflects completed paired surveys for 17 nurses at each site and is extremely feasible based on prior studies [36, 39, 40].

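### The controlled teamwork-climate regression states no term linking a professional's two surveys, which can cost precision and lets differential turnover into the interaction

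*Protocol article*

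**What the plan says.** Protocol article, Statistical analyses, Teamwork climate, sets out three analyses. The first two compare baseline with post-implementation scores, within Phase I units and then within Phase II units. Each has an unlinked and a linked version: "We will use two-sample t tests (for all professionals) and paired t tests (for professionals responding to both surveys"). The third is the only one that sets Phase I change against Phase II change: "Third, we will conduct a two group pretest-posttest analysis using multiple linear regression with teamwork score as the outcome variable". Its effect term is the unit type by period interaction, and its standard errors are robust to clustering by hospital. No professional-level term, change score or repeat-responder version is named, and no covariates are named for this model.

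Under Outcome measures, the survey goes every year to all staff of the listed professions on the study units, so membership is open. Respondents are identifiable: "Names and email addresses of professionals on study units are obtained and the survey administered by the central coordinating center using REDCap".

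Under Power and sample size, the outcome is sized on linked data: "A sample size of 68 achieves 90% power to detect a mean of paired differences of 4.0". The SD of the differences is taken as 10.0, and the test is a paired t test, two-sided at 5%. On the split over hospitals the article adds: "This sample size reflects completed paired surveys for 17 nurses at each site".

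**The concern.** The linkage is used in the two uncontrolled comparisons and is not stated for the controlled one. Read as written, the difference-in-differences regression compares whoever answered in each year, as repeated cross-sections. Two consequences follow.

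- **Precision.** Stable differences between people stay in the error. Clustering by hospital allows for within-person correlation in the standard error, because staff are nested in hospitals, but it does not recover the efficiency that a linked model would gain.
- **Composition.** If those who leave or stop responding differ in score from those who replace them, and this happens to a different degree in Phase I and Phase II units, the interaction moves although no individual's view has changed. The intervention reorganises work on the Phase I units, so such a difference is plausible. The document gives no turnover figures.

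At stake is the analysis that carries the article's claim of combined historic and concurrent control for a primary outcome.

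**Working it through.** **Inputs from the document.** Difference 4.0, SD of paired differences 10.0, two-sided 5%, 68 pairs in total (17 × 4 sites). **Assumptions, not in the document.** Within-person correlation ρ of 0.3–0.7; share p of each year's respondents who answer both surveys, 40–80%; 68 linked professionals in each unit type (the protocol does not split its 68 by phase); no extra hospital variance.

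**1. The plan's own figure.** A paired t test with difference 4.0 and SD 10 has power 89.7% at n = 67 and 90.2% at n = 68. The stated 68 reproduces, for the one-group before-after test.

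**2. Precision of the controlled contrast.** Holding the SD of differences at 10 gives a score variance s² = 100/[2(1−ρ)]. With n = 68/p respondents per year and unit type:

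- Unlinked variance = 4s²(1−pρ)/n.
- Linked variance (random intercept, generalised least squares) = 4s²(1−ρ)/{n[1−ρ(1−p)]} = 200/{n[1−ρ(1−p)]}.
- Power = Φ(4/SE − 1.96).

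Example with ρ = 0.5 and p = 0.6: s² = 100 and n = 113.3. Unlinked: 400 × 0.70/113.3 = 2.47, SE 1.57, power 72.1%. Linked: 200/(113.3 × 0.80) = 2.21, SE 1.49, power 76.8%. The variance is 11% lower. With ρ = 0.7 and p = 0.6 the SEs are 1.85 and 1.57, and the variance is 28% lower.

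Power, unlinked → linked (%):

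| ρ | p = 40% | p = 50% | p = 60% | p = 80% | p = 100% |
|---|---|---|---|---|---|
| 0.3 | 90.8 → 91.6 | 84.9 → 86.0 | 79.4 → 80.6 | 70.6 → 71.5 | 64.5 → 64.5 |
| 0.5 | 83.0 → 87.0 | 76.8 → 81.5 | 72.1 → 76.8 | 66.3 → 69.6 | 64.5 → 64.5 |
| 0.7 | 66.3 → 80.2 | 61.1 → 75.8 | 58.1 → 72.4 | 57.7 → 67.7 | 64.5 → 64.5 |

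Lower overlap means more respondents here, because the linked number is held at 68. Fixing 68 respondents per cell at 50% overlap instead gives SEs of 1.89 vs 1.86 (ρ = 0.3), 2.10 vs 1.98 (0.5) and 2.52 vs 2.13 (0.7), so the pattern is the same. At full overlap the unlinked interaction equals the difference in mean paired changes, and nothing is lost.

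**3. Composition.** Assume no true effect, turnover of 50% in Phase I and 30% in Phase II, leavers 5 points below average, joiners at the average, and ρ = 0.5.

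- *Leaving follows a stable trait.* Unlinked bias = (0.50 − 0.30) × 5 = 1.0. Simulated means: unlinked 1.02, random intercept 0.80, change score among stayers 0.00.
- *Leaving follows the year-1 score itself.* Half of the leavers' deficit would have regressed anyway, so unlinked bias = 0.20 × 5 × 0.5 = 0.5. Stayers start high and fall back: Phase I by (0.5 × 5/0.5) × 0.5 = 2.5, Phase II by (0.3 × 5/0.7) × 0.5 = 1.07, so the change-score bias = −2.5 + 1.07 = −1.43. Simulated means: unlinked 0.48, random intercept −0.03, change score −1.46.

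Turnover equal in size and selectivity gives zero in the unlinked contrast.

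**4. Precision of the change-score contrast.** SE = 10 × √(2/68) = 1.715, power 64.5%. At 60% overlap the unlinked all-respondent regression does better at ρ = 0.3 (SE 1.44, 79.4%) and at ρ = 0.5 (1.57, 72.1%), and worse at ρ = 0.7 (1.85, 58.1%).

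**The case against.** - **The article is silent; it does not say that the link is ignored.** This stands as a limit: a fuller analysis plan may add a person term. But the same paragraph specifies linkage twice and then gives the controlled model's outcome, effect term and variance estimator without it, so the stated method can fairly be improved.
- **A reader might infer that the sizing contradicts the analysis.** It does not. The sample size is for a paired t test, and a "paired t tests (for professionals responding to both surveys") is planned in each phase group.
- **The planned estimand may be the unit's climate, not individual change.** An open-cohort comparison of all staff is defensible, and a change in who stays could count as part of the effect. This is a good reason to keep the all-respondent model as the main one.
- **The paired t tests already show within-person change in each phase group.** True, but neither compares the two groups.
- **A reader might infer that comparing the same people removes turnover bias.** The document does not support that. It holds only if leaving follows a stable trait; if leaving follows the year-1 score, that contrast was the most biased of the three.

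**Conclusion.** The point holds in a limited form. The one controlled teamwork analysis states no link between a professional's surveys, although the trial already needs that link elsewhere. The cost in power is nil at full overlap, about 1 point at ρ = 0.3, 3–5 points at 0.5 and 10–15 points at 0.7, for 40–80% overlap and an assumed 68 linked professionals per unit type. Correlation, overlap and the split by phase are not in the document. Turnover that differs between unit types and is related to score moved the interaction by about 0.5–1 point in the cases tried; common turnover cancels.

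It would be too strong to say that precision is certainly lost, that the regression is necessarily biased, or that linking restores the planned power. Even fully linked, the contrast has 64.5% power with 68 pairs per unit type and 37.8% with 34, and needs 132 per unit type for 90%. That shortfall, and the reliance on four hospital clusters, are separate problems.

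**What to change.** In the third teamwork analysis, identify each professional across surveys and fit the unit type by period regression to all respondents with a professional random intercept, keeping the planned allowance for hospital. Report beside it, as a sensitivity analysis only, the year-2 minus year-1 change among professionals who answered both surveys, compared between Phase I and Phase II units.

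State what each can do. The random intercept mainly gains precision, and removes turnover bias only when leaving depends on the observed year-1 score. The change-score contrast removes it only when leaving depends on a stable trait, is open to regression to the mean otherwise, and is often less precise.

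The cost is plan wording and one extra analysis. No new data are needed, since the paired t tests already require the linkage.

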### The Advanced and Integrated MicroSystems (AIMS) interventions

The RESET project uses the Advanced and Integrated MicroSystems (AIMS) interventions, complementary and mutually reinforcing components of a redesigned clinical microsystem. The AIMS interventions address the challenges previously described and consist of 1) Unit-based Physician Teams, 2) Unit Nurse-Physician Co-leadership, 3) Enhanced Interprofessional Rounds, 4) Unit-level Performance Reports, and 5) Patient Engagement Activities. Our research team developed the AIMs interventions from available evidence, a detailed needs assessment, and our research team’s past experience implementing similar interventions [4, 26–28]. Each intervention is supported by specific processes and tools (Table 2). Importantly, many hospitals have implemented some of these interventions, but implementation is often incomplete and few have implemented all components [29].

**Table 2 Tab2:** Advanced and Integrated MicroSystems (AIMS) Interventions, Supporting Processes and Tools

Components	Descriptions	Supporting Processes and Tools
Unit-based Physician Teams	Localization of physicians to a minimal number of units on which they provide patient care	• Projecting expected patient volume • Engaging stakeholders to redesign admission processes • Monitoring progress and making adjustments
Unit Nurse-Physician Co-leadership	Collaborative model in which a nurse leader and physician leader are jointly responsible for quality improvement on their unit	• Co-leader selection and training • Co-leader job descriptions and activities • Establishing unit norms and values • Co-leader integration into mesosystem activities
Enhanced Interprofessional Rounds	Interprofessional rounds, redesigned with input from frontline professionals to optimize collaboration and patient engagement	• Redesign work groups determine timing, format, duration, and location • Discussions facilitated by unit co-leaders • Roles / expectations of attendees defined • Structured tools to support closed-loop communication
Unit-level Performance Reports	Performance reports designed to give unit leaders and frontline professionals relevant, interpretable, actionable data	• Monthly unit-level reports aligned with organizational priorities • Daily reports to identify opportunities to improve care • Just-in-time reports to identify opportunities to improve care • Teamwork Climate survey reports

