#### Adverse events

We will conduct two group pretest-posttest analyses using 2 multiple regression models. The first model will use logistic regression and the occurrence of one or more adverse events as the outcome variable (0 if patient experiences no adverse events, 1 if the patient experiences ≥1). The model will compare the change in the percentage of patients experiencing one or more adverse events from baseline to post-implementation in Phase I Implementation units to the change in Phase II Implementation units across 2 baseline periods. The model will use an interaction term defined as unit type (Phase I vs. Phase II) multiplied by the intervention period (year 1 vs. year 2) to examine the change in the outcome. (i.e., difference-in-differences analysis). We will use standard errors robust to the clustering of patients within each hospital. The second model will use Poisson regression and the number of adverse events per 1000 discharges as the outcome variable. This method accounts for episodes in which a patient may experience more than one adverse event. This model will compare the change in the number of adverse events per 1000 discharges from baseline to post-implementation in Phase I Implementation units to the change in Phase II Implementation units across 2 baseline periods. The model will use an interaction term similar to that described above (i.e., difference-in-differences analysis) and include standard errors robust to the clustering of patients within each hospital. Covariates for both models will include patient age, sex, race, payer, admission source, primary diagnosis, Elixhauser index [45], type of admission (i.e., observation vs. inpatient), and discharge destination (i.e., home vs. other).

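### The teamwork-climate difference-in-differences pools six professions and states no profession term, so a differential change in who answers could bias the interaction

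*Protocol article*

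**What the plan says.** Under Outcome measures, the protocol article sends the yearly teamwork survey "to all nurses, nurse assistants, physicians, pharmacists, social workers, and case managers on study units".

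Under Statistical analyses, Teamwork climate, there are three analyses. The first two compare before and after within Phase I units and within Phase II units. Each is done once for all respondents and once, paired, for those who answered both surveys. The third is the controlled one: "we will conduct a two group pretest-posttest analysis using multiple linear regression with teamwork score as the outcome variable". Its stated terms are unit type, period (year 1 or year 2) and their product. On errors it says: "We will use standard errors robust to the clustering of professionals within each hospital". No covariate is named, and the regression is not limited to staff who answered twice.

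Under Statistical analyses, Adverse events, covariates are listed: "Covariates for both models will include patient age, sex, race, payer, admission source, primary diagnosis", followed by a comorbidity index, admission type and discharge destination. That list belongs to the two adverse-event models only.

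Two other places bear on the point. Power and sample size, Teamwork climate, reports from prior work that "teamwork climate increases for all professionals, but the improvement is greatest for nurses", and sizes this outcome on nurses alone. Table 2 describes the first intervention component as "Localization of physicians to a minimal number of units on which they provide patient care". The Challenges section adds that sites now assign particular physicians to particular units.

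**The concern.** A difference-in-differences removes stable differences in staff mix between Phase I and Phase II units. It does not remove a change in mix that happens in one group and not, or not equally, in the other. If professions differ in their usual teamwork score, such a change moves the interaction even when nobody's view of teamwork has changed.

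The plan itself gives a reason to expect a differential change. Localization acts on the physician roster, and between years 1 and 2 it is introduced on Phase I units only. The physicians counted as working on a Phase I unit, and so invited to answer, may differ between the two surveys. Response by profession may also vary from year to year. Hospital-robust standard errors change the stated uncertainty but not the estimate.

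There is a second, separate issue. If the effect is largest in nurses, as the article expects, the pooled interaction is a mix-weighted average. The group used for planning then has no stated controlled estimate of its own.

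This regression is the only controlled analysis of teamwork climate. The other primary outcome, adverse events, has two controlled models of its own.

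**Working it through.** **The plan's own figure.** Inputs from Power and sample size: mean paired difference 4.0, standard deviation of differences 10.0, two-sided 0.05, power 90%.

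- Normal approximation: ((1.960 + 1.282) × 10/4)² = 65.7, so 66.
- Exact paired t: power 0.897 at n = 67 and 0.902 at n = 68.

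The stated 68 (17 nurses × 4 sites) is reproduced. It belongs to an uncontrolled, nurse-only paired test, so 4.0 serves below only as a rough yardstick.

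**Bias formula.** Take two groups, physicians and all others, with mean scores that differ by G and no true effect. A cell mean is the others' mean plus G × physician share. The interaction therefore has expectation

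G × [(change in physician share, Phase I) − (change in physician share, Phase II)].

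**Assumed inputs; none is in the article.** G of 5, 10 or 15 points. Physician respondents on a Phase I unit fall from 10 to 5, or from 15 to 6, beside 35 others. Phase II is unchanged.

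- 10 to 5: 5/40 − 10/45 = −0.097
- 15 to 6: 6/41 − 15/50 = −0.154

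| Gap G | Net shift −0.097 | Net shift −0.154 |
|---|---|---|
| 5 | −0.49 | −0.77 |
| 10 | −0.97 | −1.54 |
| 15 | −1.46 | −2.30 |

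Against 4.0, the extremes are 0.49/4.0 = 12% and 2.30/4.0 = 58%. The sign depends on which profession scores higher and which way the mix moves.

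**If Phase II also shifts.** The units share a hospital, so a changed roster on one may change the other. Suppose Phase II physicians fall from 10 to 8: 8/43 − 10/45 = −0.036. In the first scenario the net shift becomes −0.097 + 0.036 = −0.061, and the bias is −0.3 to −0.9 for gaps of 5 to 15.

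**What it would take to reach 4.0 by mix alone.** 4.0/G gives a net shift of 80, 40 or 20 percentage points for gaps of 5, 10 or 20.

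**Simulation check.** True effect 0, 100 respondents per cell, standard deviation 14 (assumed), 500 replicates.

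| Gap, net shift | G × shift | No profession term | With profession term |
|---|---|---|---|
| 10, 10 points | 1.0 | 1.1 | 0.1 |
| 10, 20 points | 2.0 | 2.1 | 0.1 |
| 20, 20 points | 4.0 | 3.9 | −0.1 |

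Monte Carlo error of each mean is about 14 × √(4/100)/√500 = 0.13. The adjusted values are therefore compatible with zero. That follows from the set-up, in which profession level is the only source of bias.

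**Precision.** With four hospitals, a standard deviation of 15 (assumed) and the 10-to-5 scenario, the cells hold 180, 160, 180 and 180 respondents. The unadjusted standard error is 15 × √(3/180 + 1/160) = 2.27, and 2.27 with the profession term. In the 15-to-6 scenario it is 2.18 and 2.19. Clustering is ignored in these figures, but adjustment costs essentially no precision.

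**The case against.** The strongest reply is that the article is silent and does not exclude profession. It speaks of multiple regression, it is a condensed text, and a covariate list may sit in a document not shown. A reader might infer that the authors decided to leave profession out; the text does not support that. What remains is the contrast within the article: covariates are given for one primary outcome and none for the other, so the teamwork model as written is open to this bias.

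Second, the size rests wholly on assumption. The article gives no mean score by profession, no physician counts and no response rates. Its remark about nurses concerns improvement, not level, and level drives the bias computed above. This objection stands. A reader might infer that a mix shift would manufacture or hide the full planned difference. The scenarios reach 12% to 58% of 4.0, at most about one standard error, and that yardstick is itself a nurse-only paired difference.

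Third, respondents are not a new sample each year. The plan expects repeat responders, thinks the paired nurse target easily met, and sends up to five reminders. The paired t tests hold the respondents fixed within each phase. This is a real but partial safeguard: those tests have no concurrent control and drop anyone who answered once, so they do not protect the interaction.

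Fourth, a profession main effect does not correct a change in which physicians answer, nor make a pooled effect independent of mix when effects differ by profession. Both points are right, and they shape the fix.

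**Conclusion.** The point holds in a limited form. As written, the teamwork difference-in-differences pools six professions with no stated profession term, and it is exposed to a differential change in professional mix between Phase I and Phase II units. Localization is a plausible source of such a change.

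The bias equals score gap times net change in share. It is about 0.5 to 2.3 points under assumed gaps of 5 to 15 points and assumed net shifts of about 10 to 15 percentage points with Phase II unchanged. It is smaller if Phase II shifts the same way. The documents settle neither size nor sign, so this is a case for an inexpensive safeguard and not evidence that the result will be materially wrong.

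That the pooled effect depends on mix, and that nurses have no stated controlled estimate, follows from the article's own expectation about nurses and needs no outside figure.

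**What to change.** In Statistical analyses, Teamwork climate:

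1. Add professional type (nurse, nurse assistant, physician, pharmacist, social worker, case manager, with small groups merged) as a covariate in the difference-in-differences regression.
2. Report the nurse-only interaction beside it, because the study is sized on nurses and expects the largest effect there.
3. Keep the unadjusted model as a sensitivity analysis.
4. Add, as a further sensitivity analysis, a difference-in-differences among staff who answered both surveys. It addresses a change in which physicians respond. It does not correct the mix among those who answered once, so it complements the profession term and does not replace it.

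The cost is about 3 to 5 model degrees of freedom and two short extra analyses (items 2 and 4). No new data should be needed: the survey goes to named staff defined by profession, and the paired t tests already require linking a person's two surveys.
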